## Abstract

**Background:**

About 45% of all pregnant women suffer low back pain and/or pelvic girdle pain (LBPGP). This study seeks to evaluate the effect of auricular acupuncture on LBPGP compared with placebo auricular acupuncture and with standard obstetric care in the field of primary health care.

**Methods and design:**

This study will be a four-parallel-arm, multicentre, randomised, placebo-controlled trial. A total of 212 pregnant women (24 to 36 weeks’ gestation), aged at least 17 years, with LBPGP, will be randomly assigned to the verum auricular acupuncture plus standard obstetric care group (VAAc), to the non-specific auricular acupuncture plus standard obstetric care group (NSAAc), to the non-specific placebo auricular acupuncture plus standard obstetric care group (PAAc), or the standard obstetric care group (SOC). The VAAc, NSAAc, and PAAc groups will receive treatment at three auricular acupuncture points (specific points for the VAAc group or non-specific ones for the NSAAc and PAAc groups), once a week for 2 weeks; the SOC group will receive only standard obstetric care during the same period. The primary outcome will be the reduction in pain intensity, according to the visual analogue scale (iVAS), at 2 weeks after the start of treatment. The secondary outcomes will be functional status with respect to LBPGP (according to the Roland-Morris disability questionnaire), health-related quality of life (SF12) at 2 weeks after the start of treatment, and iVAS at 12 and 48 weeks postpartum.

**Discussion:**

This trial will implement a high-quality methodology and may provide evidence for the efficacy, safety, and specificity of auricular acupuncture as a treatment for pregnant women with LBPGP.

**Trial registration:**

Current Controlled Trials ISRCTN41033073 (date 20/03/2014).

## Background

Musculoskeletal pain in pregnant women is often regarded as something that is transient, physiological, and self-limiting, but low back pain (LBP) and pelvic girdle pain (PGP) during pregnancy are associated with an increased risk of suffering these pains in future pregnancies and of the pain becoming chronic [1].

Low back pain is usually defined as occurring between the twelfth rib and the gluteal fold. Pelvic girdle pain is experienced between the posterior iliac crest and the gluteal fold, particularly in the vicinity of the sacroiliac joints. The pain may radiate to the back of the thigh and may occur in isolation or be associated with pain in the symphysis pubis [2]. Opinions are divided as to whether LBP and PGP should be associated or differentiated. According to some experts, they can be differentiated clinically, responding to different treatments and having different risk factors [3]. However, studies have so far failed to distinguish reliably between the two, and LBP is very likely to be a subgroup of the pelvic pain associated with pregnancy [4]. In fact, similar pathophysiological mechanisms – joint laxity, increased lumbar lordosis, and muscle weakness – have been suggested to be at the cause of both conditions [5-7].

About 45% of all pregnant women suffer from LBP and/or PGP (LBPGP) [8]. The prevalence appears to be somewhat higher in the Nordic countries [9], and higher still in Spain, where the prevalence at 4 weeks is estimated to be 71.3% for LBP and 64.7% for PGP [10]. LBPGP usually begins from week 18 of pregnancy, and although it may appear in the first quarter, the peak intensity is from weeks 24 to 36 [8].

There are three major risk factors for the development of LBPGP during pregnancy: strenuous work, the presence of LBP before pregnancy, and the development of LBPGP during previous pregnancies [8]. On the other hand, the use of contraceptives, the period of time elapsed since the last pregnancy, maternal height and weight, smoking, and age [2] are not usually considered risk factors, and neither the use of epidural or spinal anaesthesia or analgesia seem to be relevant [11].

LBPGP hampers women’s everyday activities, such as getting up, turning over in bed, sitting down, walking, dressing and undressing, lifting, and carrying small objects. It can also impede sexual relations, render subjects unable to work [12,13], and, in general, negatively affect their quality of life [14].

LBPGP during pregnancy is usually diagnosed in primary care, taking into account the patient’s medical history and the results of a physical examination, which will seek to exclude other causes of pain and to assess the degree of disability, as well as identifying any warning signs that could indicate the presence of inflammatory, infectious, traumatic, neoplastic or degenerative processes, that would require referral for study by other diagnostics [15]. It is unclear whether there exists any effective preventive intervention against LBPGP in pregnancy; prior studies on this question are conflicting [16,17] and, in any case, it appears that only pregnant women with previous LBP might benefit from such treatment [17].

Various therapeutic options have been proposed for pregnant women with LBPGP. The use of paracetamol is considered safe but not very effective [18]. Non-steroidal anti-inflammatory drugs do not appear to be associated with foetal malformation before 12 weeks of pregnancy [19] – although before this gestational age, few women need such medication – but are contraindicated in the third trimester of pregnancy, being associated with an increased risk of premature closure of the foetal ductus arteriosus and with oligohydramnios [20]. The association between opioid use and teratogenicity is a complicated question because the available data are contradictory and incomplete. Although data from previous studies suggest that there is no significant additional risk of congenital anomalies, there is undoubtedly a slight increase in certain heart defects, spina bifida, and, possibly, gastroschisis [21].

Prominent among non-pharmacological interventions are education, physical therapy, exercises, transcutaneous nerve stimulation, and acupuncture. The provision of specific education for pregnant women and of advice on pain-prevention strategies appears to reduce the sick leave needed by pregnant women with LBP, but not by those with PGP [3]. A recent systematic review [22] concluded that pregnant women with LBP who performed specifically adapted strengthening exercises in programmes of pelvic tilt exercises and water gymnastics reduced the intensity of LBP and the need for pain-related sick leave to a greater degree than was achieved by women who received only standard antenatal care. The same authors reported that specially designed pillows reduce pain more than normal ones, but these are not available in Spain.

Studies and reviews have supported the use of acupuncture by pregnant women with LBPGP [22,23]. Thus, it has been reported that acupuncture and stabilising exercises more effectively relieve PGP compared to standard antenatal care, and that acupuncture can provide more relief for night-time pain than is obtained by exercise alone. In a study of pregnant women with pelvic and back pain, acupuncture was found to be more effective than physiotherapy in reducing pain intensity [24]. Another study reported that 60% of pregnant women who received acupuncture suffered less intense pain, compared with 14% of those who received standard [25] antenatal care. A recent study found that acupuncture performed on women with LBPGP is more effective when applied from week 26 than during week 20 of pregnancy [26]. The adverse effects observed are minor and temporary, such as bruising, pain or swelling in the puncture site, asthenia, or nausea [25]. A recent survey showed that over 60% of pregnant women with LBPGP would accept some form of complementary therapy, including acupuncture [27].

The analgesia produced by acupuncture is caused by complex neurohormonal mechanisms involving endogenous opioids and monoamines [28], with evidence of a sustained depression of the neurons in the spinal dorsal horn [29]. Some of the effects of acupuncture may be partially explained within a conventional neurophysiological model, but there remain certain empirically-supported aspects that resist conventional explanation. Furthermore, the use of auricular acupuncture has been shown to be effective in reducing LBP in non-pregnant women [30]. Just one study published to date has evaluated the results of auricular acupuncture in pregnant women, and this paper reported that the insertion of needles in the ear for a period of one week reduces the pain and disability suffered by pregnant women with LBPGP [31]. This study was conducted in the USA and in a hospital setting. However, there have been no previous well-designed studies to evaluate the effects of auricular acupuncture in pregnant women with LBPGP compared with placebo auricular acupuncture, on the one hand, and with standard obstetric care on the other, in the field of primary health care and carried out by midwives trained in this technique. In fact, these healthcare providers have made significant contributions to studies in this field conducted by our research team [32].

### Hypothesis and study goals

Our clinical hypothesis is that acupuncture applied via pressure needles inserted in the auricle (VAAc), associated with standard obstetric care (SOC), can reduce the pain experienced by pregnant women in the lower back and/or the posterior pelvic girdle, to a greater extent than is achieved by SOC alone in the field of primary health care. Additionally, the application of this technique improves patients’ functional status and health-related quality of life, and moderates the consumption of drugs used in conventional therapy, thus reducing the associated iatrogenic effects without provoking significant iatrogenesis in itself. Secondly, VAAc applied together with SOC has specific effects, achieving a greater reduction in the LBPGP suffered by pregnant women than that achieved with the application of pressure needles at non-specific pressure points (NSAAc) or with placebo needles at non-specific points (PAAc).

The main aim of this study is to evaluate the efficacy achieved in terms of reduction in pain intensity (0 to 100 mm visual analogue scale) at 2 weeks after starting treatment. Our secondary aims are: i) to evaluate the efficacy in terms of improved functional status with respect to LBPGP (according to the Roland-Morris disability questionnaire) at two weeks after starting treatment; ii) to evaluate the efficacy in terms of improved health-related quality of life (SF12) at two weeks after starting treatment; iii) to evaluate the efficacy in terms of improvement perceived by the patient with LBPGP at two weeks after starting treatment; iv) to evaluate the impact on temporary occupational incapacity of pregnant women with LBPGP; v) to evaluate the efficacy in terms of reduced consumption of analgesic medication at 2 weeks after starting treatment; vi) to evaluate the presence of LBPGP at 12 weeks postpartum; vii) to evaluate the presence of LBPGP at 48 weeks postpartum; and viii) to estimate the placebo effect and the specific and non-specific effects of VAAc, NSAAc, and PAAc.

## Methods/design

### Design

Multicentre prospective randomised controlled study, with four parallel arms, to compare acupuncture with pressure needles inserted in the ear (VAAc) together with SOC; non-specific auricular acupuncture plus SOC (NSAAc); non-specific placebo acupuncture plus SOC (PAAc); and SOC alone (Figure 1). The results will be analysed by statisticians blinded with regard to the allocation of patients to the different treatment groups.

**Figure 1 F1:**
[figure not shown]
Trial flow.

### Study period

February 2014 to December 2016.

### Study scope and subjects

The study population will be composed of pregnant women (24 to 36 weeks’ gestation), aged 17 years or more, referred by their family physicians from the 21 primary care centres participating in the study, belonging to the Andalusian Public Health System and located in the provinces of Seville and Málaga, diagnosed with pregnancy-related LBPGP and who have not previously received auricular acupuncture. Women with LBPGP that began before the pregnancy, or presenting any of the ‘red flags’, which would require examination to rule out the possible presence of LBPGP secondary to inflammatory, infectious, traumatic, neoplastic, or degenerative processes, together with women receiving anticoagulant treatment or presenting dermatitis of the auricle, will be excluded from the study.

The women will be given the following information: “*This study is being conducted to compare the effects of standard obstetric care either alone or in conjunction with one of three types of stimulation of the ear (auricular acupuncture). One of these is similar to traditional Chinese auricular acupuncture, while the others do not follow these principles. One is a placebo intervention, but all have been associated with positive outcomes in various clinical studies*”. The women will also be informed of the potential risks associated with different types of auricular acupuncture (infection, pain at the puncture site, fainting, bruising) and that they may terminate their participation in the study at any time without any penalty or loss of the benefits to which they are entitled. All study participants must sign the informed consent form.

### Randomisation and blinding procedures

The four study arms will be randomised centrally, at the Costa del Sol Hospital, Research Support Unit, to achieve a 1:1:1:1 allocation ratio, stratified by healthcare centre. The health professionals taking part in the study will not be involved in the randomisation process. Patients who meet the inclusion criteria and give their signed informed consent will be included in the study. After inclusion, the researcher will contact the randomisation centre, where the patient’s data will be recorded, and the midwife will be informed, by telephone and by fax, of the patient’s allocation to one of the four study arms. This procedure ensures that randomisation will not be influenced by any of the researchers involved. The patients assigned to the VAAc, NSAAc, and PAAc groups will be blinded with respect to the treatment allocated to them.

### Treatment

A 4-hour workshop will be organised for all the midwives participating in the study to demonstrate the implementation of the technique, the obstetric care to be provided, and the study records to be kept. The workshop will be given by two physicians who are specialists in acupuncture and have over 10 years’ clinical experience. At one month after initiating the study, a test will be applied to confirm that the skills acquired in the workshop are retained.

#### Standard obstetric care (SOC)

The SOC for the treatment of LBPGP in pregnancy will include an explanation of its cause and of recommended self-care procedures, both to prevent pain and to reduce its intensity, together with training in specific stretching exercises for the back and the hamstrings. In addition, the women participating in the study will be recommended to use paracetamol and/or visit their family doctor if the pain intensity becomes severe.

#### Verum auricular acupuncture (VAAc)

Auricular pressure needles 1.5 mm long and 0.20 mm in diameter (Pyonex Seirin, Shizuoka, Japan) (Figure 2) will be applied to two standardised points (Shenmen and Kidney), and at a reflex point in the region of the auricle that classically represents the lumbar or sacral regions [33], and which will be detected by means of a probe calibrated at 250 g of pressure (Figure 3). The points will be located in a single ear, preferably the one on the side of the body corresponding to the location of the pain; if the pain is bilateral, the most sensitive ear will be determined by using a probe to exert a pressure of 250 g. Before placing the implants, the ear will be disinfected using chlorhexidine. The patients will be instructed not to exert pressure on the implants at any time.

**Figure 2 F2:**
[figure not shown]
Auricular device used for the verum auricular acupuncture and non-specific auricular acupuncture (New Pyonex) groups and for the placebo auricular acupuncture group.

**Figure 3 F3:**
[figure not shown]
Specific and non-specific auricular acupuncture points used for the different study groups.

#### Non-specific auricular acupuncture (NSAAc)

The needles used in the non-specific auricular acupuncture group will be the same as in the VAAc group, but they will be applied at auricular points that are non-specific for LBPGP, and which instead correspond to anatomic locations in the ankle, wrist, and shoulder (Figure 3).

#### Placebo acupuncture (PAAc)

The devices used in the placebo group will be supplied by Seirin (Pyonex Placebo, Seirin, Shizuoka, Japan) and by 3B Scientific (Spain). They will be identical to those used in the VAAc group, but without the needle [34] (Figure 2), and will be applied at the same non-specific points as for the NSAAc group.

#### Data sourcing and compilation

We have designed a data form on which the variables of interest should be entered by the researcher at each centre. The baseline assessment (T0), intermediate result at one week (T1), end result at two weeks (T2), follow-up at 12 weeks postpartum (T3), and follow-up at 48 weeks postpartum (T4) will be performed by the midwives taking part in the study, who may also instruct the patients on how to complete the self-administered questionnaire. The information will be electronically recorded and stored, at a single coordinating point for each province, in a database for subsequent statistical analysis. Data collection will be conducted in person, at times T0, T1, T2, and T3. Only the evaluation at T4 will be carried out by telephone. Patient confidentiality will be maintained by removing patient identity data from the database. Figure 1 summarises the flow plan for the study.

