In addition, data will be recorded for pain intensity, location (lower back, posterior pelvis or both, and whether pain is radiating to the leg), onset, and frequency of pain (occasional days, nearly every day, every day). Pain intensity will be measured by a visual analogue scale (iVAS) at T0, T1, and T2, as well as at the follow-up assessments T3 and T4. There is ample evidence supporting the validity of the iVAS for pain intensity, and many studies have corroborated its construct validity [35] and reliability [36,37]. It is a simple and fast method to assess subjective pain intensity. The patient is asked to mark on a 100-mm scale from 0 (no pain) to 100 (worst pain imaginable) the intensity of back pain by day (iVASd) and night (iVASn). The primary outcome, the change in pain intensity (iVAS) at 2 weeks after the start of treatment (T2), will be determined from the maximum value of the daytime pain measurements (iVASd) or the night-time ones (iVASn) at 2 weeks after starting treatment. There is evidence that reductions of greater than 35 mm on this scale are associated with an improvement perceived by the patient [38].

The women taking part in the study will be asked to complete the Roland-Morris disability questionnaire to assess the level of disability provoked by LBPGP at T0 and at T2. This self-administered questionnaire has been validated for use in Spain [39] and consists of 24 questions or statements related to incapacity caused by LBP. Respondents are asked to award one point for each statement that corresponds to their current situation. Scoring is quick and easy: the total score awarded may range from 0 points (no incapacity caused by LBP) to 24 (maximum incapacity). Changes in health-related quality of life are valued according to the SF-12 v.2 self-administered questionnaire. This is a generic questionnaire, derived from SF-36, which has been validated for use in Spain [35]. Version 2 allows the researcher to calculate the respondent’s quality of life in eight domains (physical function, physical role, pain, general health, vitality, social function, emotional role, mental health) and two summary components (physical and mental). A version with six items, to enable the calculation of utilities, is currently being validated. In our study, this would enable a cost-effectiveness analysis to be conducted.

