We will also evaluate the consumption of analgesic medication, whether or not prescribed by the patient’s doctor, both at the time of randomisation (T0) and at final assessment (T2), according to a 4-point Likert scale of 0–3: (0) = none, (1) = less than the usual dose, (2) = usual daily dose, and (3) = greater than the usual dose. We will also record the names of the medications taken and the daily dose in each case.

The Treatment Credibility Scale [43] will be used to evaluate patients’ expectations and the credibility of the treatments provided in the study. The original Borkovec and Nau scale [44] with four items will be applied, assessing the following questions on a continuous VAS of 0 to 10 (0 to 10, from totally disagree to totally agree): (1) = Are you confident that this treatment can alleviate your pain? (2) = Does it seem a logical treatment? (3) = Would you recommend this treatment to a friend or family member who was suffering the same problem? (4) = Do you think this treatment would be an option for treating other problems? Questions 1 and 2 will be assessed after the first treatment session, and questions 3 and 4, after 2 weeks.

After the treatment has concluded, the blinding of the patients’ allocation to one of the two auricular acupuncture groups (real or placebo) will be verified by the following dichotomous question: Do you think you were assigned to the real auricular acupuncture group or to the placebo group?

During the study, side effects and possible adverse reactions resulting from the treatment will be recorded.

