## Discussion

When auricular acupuncture is practiced according to the principles of Traditional Chinese Medicine, it is an individualised treatment. In this study we have designed a semi-standardised treatment protocol that approximates standard clinical practice, which is sufficiently flexible and straightforward so that it can be performed by midwives without prior training, and which enables reproducibility.

As this experimental study is designed to be applied by medical personnel whose training is limited to an intensive 4-hour course in the technique, obviously the auricular acupuncture treatment cannot be performed to its full extent. For this reason, we have limited the number of points where acupuncture needles will be applied, and therefore the therapeutic effect obtained may be less than that otherwise to be expected. This limitation will produce an effect contrary to the study hypothesis.

Moreover, the patients assigned to the PAAc and NSAAc groups, due to the healthcare provided and the effects of dermatological stimulation, however minimal, may achieve some positive results. This effect, too, is contrary to the study hypothesis, but to a certain extent will reflect the non-specific effect of the intervention.

A double-blind study cannot be carried out because the therapist must know which treatment is being applied. We have attempted to minimise the consequences of this situation by ensuring that the professional who provides the treatment does not intervene in the assessment of the outcome. Furthermore, the blinding of the evaluators and the patients is designed to be highly effective. In addition, a question will be included to determine the patients’ perceptions regarding the type of auricular acupuncture received. Since the main outcome variable and many of the secondary ones will be recorded by means of a self-administered questionnaire no added bias will be caused by the intervention of the midwife in this area.

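### The Discussion claims separate, blinded outcome assessors whom the described procedures do not provide, and no method is given for taking a marked 100-mm pain score by telephone at 48 weeks

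*Protocol article*

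**What the plan says.** All references are to the protocol article.

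- **Treatment:** "A 4-hour workshop will be organised for all the midwives participating in the study to demonstrate the implementation of the technique". The Discussion adds that the protocol is simple enough that "it can be performed by midwives without prior training".
- **Randomisation and blinding procedures:** after inclusion, "the midwife will be informed, by telephone and by fax, of the patient’s allocation to one of the four study arms". Only women in the three auricular arms (VAAc, NSAAc, PAAc) are listed as blinded. SOC is not.
- **Data sourcing and compilation:** assessments T0, T1, T2, T3 and T4 "will be performed by the midwives taking part in the study, who may also instruct the patients on how to complete the self-administered questionnaire". On the mode of contact: "Only the evaluation at T4 will be carried out by telephone".
- **Variables:** pain intensity (iVAS) is measured at all five time points, and its 48-week score is a listed secondary outcome. On completing it: "The patient is asked to mark on a 100-mm scale". The check on patient blinding for "one of the two auricular acupuncture groups (real or placebo) will be verified by the following dichotomous question".
- **Discussion:** the consequences of an unblinded therapist are said to be reduced by "ensuring that the professional who provides the treatment does not intervene in the assessment of the outcome". The evaluators are described as blinded. Because the main outcome and many secondary ones are self-completed, the midwife is said to add no bias there.

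**The concern.** The outcomes are largely subjective, and the person who applies the device knows the arm. Who collects the outcome data is therefore a central validity claim. A reader of the Discussion would credit the trial with an assessor who is separate from treatment and unaware of allocation. The operational sections name only the participating midwives, who are trained to treat, and the midwife is told the arm.

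Two related gaps follow.

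- The 48-week iVAS is defined as a mark on a line but is to be collected by telephone, with no procedure stated. If the answer is spoken, it is no longer self-administered, and the Discussion's defence does not reach it.
- The patient-blinding question is framed around two auricular groups, although there are three. Women in NSAAc receive real needles at non-specific points and fit neither label cleanly.

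**Working it through.** The point rests on comparing passages, so the main steps are textual.

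1. **Who treats?** The Background describes the technique as delivered by trained midwives. The Treatment section trains all participating midwives in it, and the Discussion presents it as suited to midwives. The treating staff are therefore drawn from the participating midwives.
2. **Who knows the arm?** Randomisation and blinding procedures: the midwife is told it by telephone and fax, after inclusion.
3. **Who assesses?** Data sourcing and compilation: the participating midwives, at all five time points, with permission to explain the questionnaire.
4. **Who is the blinded evaluator?** None is named. The Design and Ethical issues sections blind the statisticians. That protects the analysis, not data collection.
5. **Result of 1 to 4 against the Discussion.** Treaters and assessors are described as the same group of staff. No split within that group is described, and no masking of an assessor.
6. **How far does self-completion help?** By the Discussion's own wording it covers the main outcome and many, not all, of the secondary ones. It concedes that the midwife is involved. The primary comparison is VAAc versus SOC (Sample size; Statistical analysis). SOC women know they have no ear device, so self-report protects this contrast least.
7. **T4.** Mode: telephone. Measure: a mark on a 100-mm scale. Status: secondary outcome. No telephone version and no posted form is described. The Statistical analysis section names a test for presence of pain at 48 weeks, which can be asked by telephone, but none specifically for the 48-week iVAS.
8. **Blinding question.** It is asked after treatment ends, so before T3 and T4. It has two answers for three arms.
9. **Size.** The plan's sample size is not in dispute and reproduces: 2 × (25 × (2.576 + 1.282) / 20)² = 46.5, so 47 per group; 47 / 0.9 = 52.2, so 53; 4 × 53 = 212. The same inputs give the smallest observed VAAc–SOC difference that reaches two-sided P < 0.01 with 47 per group: 2.63 × 25 × √(2/47) = 13.6 mm. This is only a yardstick. The document gives nothing from which a bias in millimetres could be set against it.

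**The case against.** The strongest reply is that the two sections can be reconciled. Data sourcing and compilation speaks of the midwives collectively, across 21 centres. A colleague who has not treated the woman, and perhaps has not been told her arm, could assess her, and a condensed article may leave that arrangement to the full protocol. This stands as far as it goes. A reader might infer that each woman's own midwife assesses her, but the text does not say so. Nor does it describe the split that would make the Discussion true.

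Other stronger readings also lack support:

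- **Steering of answers.** The midwives may explain how to fill in the form. Nothing says that they influence its content.
- **Every visit affected.** The midwife learns the arm only after inclusion, so T0 may precede allocation.
- **The 48-week iVAS is unobtainable or biased between arms.** A posted paper scale would be possible. All arms share the telephone mode, so the change of mode alone does not bias the comparison between arms. The primary outcome is taken in person at two weeks.
- **Blinding cannot be judged in NSAAc.** The proportion guessing real treatment can still be compared across the three arms.

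The Discussion's self-completion argument does reduce the risk for the primary outcome. It does not make an evaluator blinded, and it does not cover a telephone interview.

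Any remedy has limits too. Recruitment is under way, so procedures would change partway through. No change to assessment can blind SOC women.

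**Conclusion.** The point holds as an internal contradiction. The Discussion claims separation of treater from assessor and blinding of evaluators, and the described procedures provide neither. It also holds that no procedure is given for obtaining the 48-week iVAS by telephone. The two-group wording of the blinding question is a minor error.

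The assessor problem concerns assessments made after allocation, T1 to T4. The scale problem concerns T4 only, and one secondary outcome. The size of any bias cannot be computed from the document, and none is asserted here. The conclusion assumes that the article describes the assessment arrangements as they are. If the full protocol names assessors who do not treat and do not hold the allocation, the remedy on this part is to say so in the article.

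**What to change.** 1. From T1 to T3, have the woman complete and seal her forms before she meets the treating midwife. Give instruction on the forms only at T0, before allocation.
2. Have the T4 calls made by existing staff who do not hold the allocation.
3. State the T4 pain measure. Either use a verbal 0–100 rating, collected also at T3 for women not yet past that visit, or post a paper scale before the call. Report T4 as the measure actually used.
4. Correct the Discussion so that it claims no assessor blinding beyond what is done, and acknowledge that SOC women are unblinded.
5. Minor: correct the reference to two auricular groups, add a do-not-know answer, and tabulate guesses for each of the three arms. The question should not describe the placebo device. It is asked before T3 and T4, and the quoted patient information does not reveal that the placebo has no needle.

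Cost: changed form wording, envelopes, and calls reassigned among existing staff, with no new visits and no change to sample size. The downside is a mix of procedures before and after the change, so its date should be recorded. A T3 verbal rating will be missing for women already past that visit.
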